## Abstract

**Background:**

Pregnancy-related anaemia is a public health challenge across Africa. Over 50% of pregnant women in Africa get diagnosed with this condition, and up to 75% of these are caused by iron deficiency. The condition is a significant contributor to the high maternal deaths across the continent and, in particular, Nigeria, which accounts for about 34% of global maternal deaths. Whereas oral iron is the mainstay treatment for pregnancy-related anaemia in Nigeria, this treatment is not very effective given the slow absorption of the medication, and its gastrointestinal adverse effects which lead to poor compliance by women. Intravenous iron is an alternative therapy which can rapidly replenish iron stores, but fears of anaphylactic reactions, as well as several misconceptions, have inhibited its routine use. Newer and safer intravenous iron formulations, such as ferric carboxymaltose, present an opportunity to overcome some concerns relating to adherence. Routine use of this formulation will, however, require addressing misconceptions and systemic barriers to adoption in the continuum of care of obstetric women from screening to treatment. This study aims to test the options to strengthen routine screening for anaemia during and immediately after pregnancy, as well as evaluate and improve conditions necessary to deliver ferric carboxymaltose to pregnant and postpartum women with moderate to severe anaemia.

**Methods:**

This study will be conducted in a cluster of six health facilities in Lagos State, Nigeria. The study will employ continuous quality improvement through the Diagnose-Intervene-Verify-Adjust framework and Tanahashi’s model for health system evaluation to identify and improve systemic bottlenecks to the adoption and implementation of the intervention. Participatory Action Research will be employed to engage health system actors, health services users, and other stakeholders to facilitate change. Evaluation will be guided by the consolidated framework for implementation research and the normalisation process theory.

**Discussion:**

We expect the study to evolve transferable knowledge on barriers and facilitators to the routine use of intravenous iron that will inform scale-up across Nigeria, as well as the adoption of the intervention and strategies in other countries across Africa.

**Supplementary Information:**

The online version contains supplementary material available at 10.1186/s43058-023-00400-y.

Contributions to the literature
This implementation research is expected to contribute to both contextual and generalisable knowledge on how to adopt and scale up the use of intravenous ferric carboxymaltose for treating obstetric cases of iron deficiency anaemia in Africa.Incorporating the Tanahashi health systems model into the Diagnose-Intervene-Verify-Adjust (DIVA) model, an adaptation of the Deming cycle, will demonstrate the application of systems thinking in quality improvement in resource-constrained health system contexts.Lessons learned from the methodological approach used in this study are expected to build capacity and advance the application of implementation science to strengthen health systems in Africa and beyond.

## Background

Anaemia in pregnancy (haemoglobin (Hb) levels less than 11.0g/dL) is a major public health burden with a higher incidence in low- and middle-income countries (LMICs) [1]. An estimated 31–52% of pregnant women in Africa will experience anaemia [2]. Iron deficiency accounts for 50–75% of these cases [3]. The common causes of pregnancy-related anaemia in Africa include nutritional disorders, malaria, infections, haemoglobinopathies, haemorrhage, and chronic diseases [4]. The condition is associated with an increased risk of morbidity and mortality for the mother and the baby during pregnancy and postpartum. Common complications related to anaemia in pregnant and postpartum women include low birthweight, preterm birth, postpartum haemorrhage, maternal depression and other psychosocial events, stillbirth, and neonatal mortality [5, 6].

The World Health Organization (WHO) recommends Hb testing at each trimester of pregnancy as a proxy screening for iron deficiency anaemia [7]. After delivery, Hb levels should be measured within 24 to 48 h in women with blood loss above 500 mL, women with uncorrected anaemia diagnosed within antepartum, or women exhibiting signs and symptoms suggestive of anaemia postnatally [7, 8]. The WHO classifies anaemia during pregnancy and puerperium (the first 6 weeks after childbirth during which the mother’s reproductive organs return to their original nonpregnant state) into three categories of severity: (1) mild anaemia (Hb levels 9 to 10.9 g/dL), (2) moderate anaemia (Hb levels 7.0 to 8.9 g/dL), and (3) severe anaemia (Hb levels less than 7.0 g/dL) [9].

Current WHO guidelines recommend that women diagnosed with obstetric anaemias should be treated with high-dose oral iron at 120 mg of elemental iron daily until Hb rises to normal (Hb 11.0 g/dL or higher) [7]. However, oral iron, though cheap, usually takes several months of treatment to correct anaemia and replenish iron stores [10]. Also, about 70% of patients on oral iron (particularly ferrous sulphate) experience gastrointestinal adverse effects such as vomiting, constipation, diarrhoea, and abdominal pain [10–12]. These adverse effects are often due to unabsorbed iron and ultimately limit treatment adherence, further posing a challenge to achieving optimum correction of anaemia by the end of the puerperium. As an alternative, some intravenous iron preparations can be given as a single dose and are suitable for patients who respond poorly to oral iron and moderately anaemic women that require more rapid iron replacement for symptom control [8]. Intravenous iron corrects anaemia faster and in fewer doses than oral iron, requiring less patient-provider interaction [8]. This situation is ideal in LMICs where the loss to follow-up is common for various reasons, especially in the postpartum period [13, 14]. Intravenous iron administration presents an opportunity to rapidly treat moderate and severe anaemia during pregnancy, thereby minimising the risk of poor maternal, foetal, and newborn outcomes.

Nigeria accounts for about 34% of global maternal deaths [15] and has a high prevalence of iron deficiency anaemia among pregnant women ranging from 25 to 45.6% [16]. Whereas clinicians know of intravenous iron, its use is not widespread for treating pregnancy-related iron deficiency anaemia [17]. This may be due to common misconceptions about the treatment modalities for iron deficiency anaemia, which have been reported in similar settings to Nigeria [10]. One of these misconceptions is that oral iron is always effective if patients tolerate high daily doses. However, the recommended thrice daily dosing to treat mild to moderate anaemia in pregnancy is associated with poor adherence [18, 19], with compliance rates in Nigeria estimated to be as low as 65% [19]. Another common misconception is that intravenous iron is associated with a high risk of anaphylaxis and may increase the risks of infection and oxidative stress and should be restricted to severe cases of anaemia [10]. Contrary to this assumption, evidence suggests a shallow risk of life-threatening allergic reactions with all intravenous iron formulations [10]. Furthermore, data from meta-analyses and large observational studies show that, in comparison with oral iron or no iron, short-term intravenous iron therapy does not present an increased risk of infection [10, 20, 21].

Newer intravenous (IV) iron formulations, such as ferric carboxymaltose (FCM), which have fewer adverse effects than high-molecular weight iron dextran and has been demonstrated to be better tolerated than many other intravenous iron preparations, as well as oral iron, are now available [22]. A single high dose of FCM can be infused in 15 min, rapidly replenishing iron stores [23]. FCM has also been demonstrated to be cost-effective in correcting anaemia in comparison with the use of red blood cell transfusion [24], IV iron sucrose [25, 26], and ferric derisomaltose [26]. One study in the UK concludes that FCM is likely to be the least costly and most effective IV iron therapy available [26].

FCM has potential promise in treating obstetric anaemias in Nigeria and many other LMICs. In Nigeria, pregnant women seek antenatal care relatively late, with most first-time visits in the middle to the late second trimester, and less than 60% attend the recommended four or more antenatal visits [27]. The implication is that the detection of anaemia is also often late. Thus, FCM may be more effective than oral iron in Nigeria, even though the formulation is not yet on the essential drug list [28]. The IV versus oral iron clinical trials are ongoing to test this hypothesis in pregnancy (IVON trial) [12] and postpartum (IVON-PP trial ISRCTN51426226). This proposed implementation science research (IVON-IS) seeks to complement the IVON and IVON-PP trials by using continuous quality improvement and participatory action research to evolve and test strategies to strengthen existing diagnostic processes for anaemia in pregnancy and postpartum. The study will also test strategies to strengthen referral pathways and facilitate the routine treatment of moderate to severe anaemia with FCM within Nigeria’s health system.

Specifically, the objectives of the study are to:Identify opportunities and strategies to routinise and strengthen screening for anaemia to identify and target pregnant and postpartum women who stand to benefit from intravenous FCM administrationIdentify health system capacity needs at different levels required for FCM administration during pregnancy and options for immediate postpartum administrationIdentify potential care and referral pathways and understand the barriers and facilitators to uptake and user experiencesDevelop, test, and iterate strategies for improving the screening process for anaemia and FCM administration within the existing health system.

## Methods

The study adheres to the Standards for Reporting Implementation Studies (StaRI) statement and checklists from the EQUATOR network [29, 30] (see Additional file 1). The timelines for the study are presented in Fig. 1.

**Fig. 1 Fig1:**
[figure not shown]
Proposed 36-month study timeline

### Study setting

IVON-IS will be conducted in Lagos State, South West, Nigeria. Specifically, implementation outcomes will be tested in a cluster of six health facilities that have not yet been exposed to training or implementation related to the ongoing IVON trials. The facilities span public (government-owned) and private (individual/organisation-owed) sectors in the state. The cluster will include one tertiary hospital, two secondary hospitals, one comprehensive primary health centre (PHC) in the public sector, and two private hospitals with varied patient bases. The selected facilities will be in proximity and linked to the state’s existing referral process. The cluster will represent a sub-unit of the health system and reflect the points of antenatal and postnatal care for pregnant women. Indeed, in Lagos, public health facilities manage 27% of deliveries in the state, while private health facilities take up about 48% [27]. Using projected data from our ongoing IVON clinical trials, we estimate that we will screen about 4000 pregnant and postpartum women per annum and have approximately 400 women eligible for treatment for anaemia.

### Study interventions and implementation processes

The IVON-IS will aim to test the routine implementation of two interventions along the management pathway for anaemia in pregnancy and postpartum (i.e. screening for anaemia and treating anaemia using FCM). The study will also examine the linkages and interactions of patients, health system actors, and processes within and between health facilities as women transition through the health system (Fig. 2).

**Fig. 2 Fig2:**
[figure not shown]
Scope of the IVON implementation research

### Implementation strategy

Continuous quality improvement, which incorporates the Tanahashi model for health system evaluation and a variant of the Plan-Do-Study-Act (PDSA) cycle known as the Diagnose-Intervene-Verify-Adjust (DIVA) model will be employed to identify and improve implementation bottlenecks using participatory approaches (Fig. 3). Tanahashi’s model for health service coverage emphasises the quality and effectiveness when attaining an equitable and effective coverage [31, 32]. DIVA has been successfully applied to identify and improve bottlenecks in decentralised health systems across sub-Saharan Africa, including Nigeria [31, 33, 34]. For our study, DIVA will be implemented in quarterly cycles.

**Fig. 3 Fig3:**
[figure not shown]
The DIVA Cycle

An implementation management team (IMT) comprising health system actors (health care providers, health services managers, policymakers), health services users/interest groups (patients, families, community/ward development committees), and academic researchers will be convened. We will commence with an introductory meeting with the IMT. This will be followed by a pre-implementation training of the IMT on the bottleneck analysis approach and tools. The bottleneck analysis approach identifies barriers to effective coverage of healthcare services and develops strategies for improvement. Bottleneck analysis workshops will be conducted quarterly during the implementation of the project. The IMT will undertake activities to:Understand and document what anaemia screening and treatment currently look like and what the patient journeys are, considering the levels of the health system and facility and staffing requirements across the care cascade (e.g. testing, referral, treatment, follow-up)Identify elements that need to be strengthened and levels at which new strategies for screening, referral, and various anaemia treatment modalities, such as iron-folic acid and intermittent preventive treatment of malaria during pregnancy, can be introducedCo-design new strategies with key stakeholders, including government officials, along with an implementation framework that articulates key implementation-related questionsTest approaches for implementing co-developed context-sensitive strategies using pre-designed evaluation methods for comparison and iterationUnderstand and document user experiences, as well as key barriers and facilitators to anaemia screening and testing

#### DIVA processes and outcomes

The outcomes of interest will be informed by Tanahashi’s model for health system evaluation [32]. Tanahashi argued that health care coverage should not measure the percentage number of people reached but rather measure the percentage of the number of people who received quality service. He then proposed a model to identify and address the barriers to improving effective coverage of interventions. The Tanahashi model consists of five domains (Fig. 4):Availability coverage: availability of human resources and essential commoditiesAccessibility coverage: accessibility of distribution points for interventionsAcceptability coverage: proportion of the population willing to use the serviceContact coverage: proportion of the target population who use the serviceEffective/quality coverage: proportion of the target population who received quality and/or satisfactory service

**Fig. 4 Fig4:**
[figure not shown]
Adapted from the Tanahashi model for health system evaluation

During the ‘diagnose’ phase of DIVA, the IMT will conduct bottleneck analyses across the Tanahashi model domains to identify constraints to effective coverage of the interventions (preventive, diagnostic, and management modalities). The difference between target coverage and observed coverage for each domain indicator will be identified as a measure of the bottleneck.

Using techniques and tools like brainstorming, the ‘5 whys’ technique, affinity, and driver diagrams, we will guide the IMT to identify immediate, proximal, and distal causes of identified bottlenecks. This step is known as a root cause/causal analysis. In the ‘intervene’ phase, the IMT will brainstorm plausible solutions and strategies to address these bottlenecks. Subsequently, proffered strategies will be converted into action plans along with specific quality/coverage targets for the next implementation quarter. During the ‘verify’ phase, the implementation of planned activities will be monitored through existing supportive supervision, monitoring, and evaluation mechanisms year-round. This will help the early detection of deviation or lag while also optimising the implementation fidelity of planned activities. At any point during verification, implementation challenges identified will be addressed to ensure strategies are carried out as planned and are on track towards attaining targets within stipulated time frames. This forms the ‘adjust’ phase [33, 34] (Fig. 5).

**Fig. 5 Fig5:**
[figure not shown]
The process framework for bottleneck identification, analysis, and improvement

#### DIVA outcome measures

Table 1 highlights the study indicators to be quantitatively monitored and improved. The primary outcome of the DIVA process will be the improvement in the implementation fidelity (effective coverage) to the three management processes along the continuum of care as depicted in the scope (Fig. 2). These are:Process of screening for anaemia in pregnancy and postpartumSupport along the care and referral pathway following diagnosis of anaemia in pregnancy and postpartumProcedural guide for the infusion of IV ferric carboxymaltose (as deployed in the IVON trial)

**Table 1 Tab1:** Outcome measures and indicators to be monitored and improved

Tanahashi model domain	IVON-IS outcome measure	Operational definition		
		Preventive/promotive care	Existing management procedures	FCM treatment
Availability coverage	Trained human resource availability	The proportion of target health workers at each site who have been trained on the screening and other preventive care protocols for antepartum and postpartum anaemia (including health education and nutrition)	The proportion of target health workers at each site who have been trained on the screening and management protocols for antepartum and postpartum anaemia (including preventive, promotive, diagnostic, and treatment)	The proportion of target health workers at each site who have been trained in administering FCM. These health workers are from health facilities that have not yet been exposed to training or implementation of IV FCM.
Accessibility coverage	Service accessibility	The proportion of women attending antenatal and postnatal clinics who were offered screening and promotive care	The proportion of women diagnosed with anaemia who were prescribed treatment for anaemia	The proportion of women eligible to receive the IV FCM for pregnancy and/or postpartum anaemia who were offered the infusion.
Acceptability coverage	Acceptability	The proportion of eligible women who were screened and who utilised other promotive care provided	The proportion of eligible women who used the prescribed treatment option	The proportion of women eligible to receive the IV FCM for pregnancy and/or postpartum anaemia who consented to receive the infusion
Contact coverage	Service utilisation	Same with acceptability	Same with acceptability	The proportion of women eligible to receive the IV FCM for pregnancy and/or postpartum anaemia who were administered the infusion irrespective of the protocols.
Effective/quality coverage^a^	Implementation fidelity	The proportion of eligible women screened for anaemia who adhered to the post-screening plan (e.g. referral for treatment of diagnosed anaemia or prescribed nutritional supplements)	The proportion of women with anaemia who used the treatment option according to the prescribed plan (e.g. dose/duration)	The proportion of women eligible to receive the IV FCM for pregnancy and/or postpartum anaemia who were administered the infusion according to the protocols.

^a^Primary outcome of DIVA

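### Table 1 measures acceptability as use in two of its three columns and leaves supplies out of availability, so the bottleneck measure cannot separate unwilling from unserved women or directly show a shortage

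*Protocol article*

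**What the plan says.** The section *DIVA processes and outcomes* lists five coverage domains. Three matter here: availability covers both staff and essential supplies, acceptability is the share of people willing to use the service, and contact is the share of the target population who use it.

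Table 1, under *DIVA outcome measures*, turns these domains into indicators for three columns:

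- **Availability.** The outcome measure is "Trained human resource availability". All three cells count trained workers. The FCM cell, for example, reads "The proportion of target health workers at each site who have been trained in administering FCM".
- **Acceptability.** The preventive/promotive cell is "The proportion of eligible women who were screened and who utilised other promotive care provided". The existing-management cell is "The proportion of eligible women who used the prescribed treatment option". The FCM cell counts eligible women "who consented to receive the infusion".
- **Contact.** The first two columns say "Same with acceptability". The FCM cell counts eligible women "who were administered the infusion irrespective of the protocols".

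The text after Fig. 4 says how the indicators are used: "The difference between target coverage and observed coverage for each domain indicator will be identified as a measure of the bottleneck". Root-cause analysis of the bottlenecks so identified follows, in quarterly cycles.

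**The concern.** The article's own definitions and its own operational table disagree. Where acceptability is recorded as use, a woman who agreed to a test or treatment but did not get it is scored as a shortfall in acceptability. Willingness itself is not measured in those two columns. Likewise, a site with every worker trained and no test supplies can score 100% on availability.

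The purpose of the coverage model is to show at which step women are lost. The step at which a gap appears is the starting point for each quarter's causal analysis and action plan. If refusal, service failure and supply failure share one number, that starting point may be wrong. Supply is a foreseeable constraint: the *Background* notes that FCM is outside Nigeria's essential drug list.

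**Working it through.** The plan gives no figure to reproduce on this point. The check compares the definitions with the indicators and then applies the plan's bottleneck rule.

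**Step 1. Definitions against indicators.**

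| Domain | Defined in *DIVA processes and outcomes* as | Preventive/promotive | Existing management | FCM |
|---|---|---|---|---|
| Availability | staff and supplies | trained staff only | trained staff only | trained staff only |
| Acceptability | willingness | use | use | consent |
| Contact | use | same as acceptability | same as acceptability | administration |

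Five domains by three columns give 15 cells. Two duplicate another cell, so 15 − 2 = 13 are distinct. Cells that measure stock: 0.

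**Step 2. The bottleneck rule.** Gap = target − observed. The article gives no values, so these are assumed: a target of 80% for both domains, true use of 60%, and true willingness of 60%, 75% or 90%.

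| True willingness | Table 1: acceptability gap | Table 1: contact gap | As defined: acceptability gap | As defined: contact gap | As defined: willingness − use |
|---|---|---|---|---|---|
| 60% | 80 − 60 = 20 | 20 | 80 − 60 = 20 | 20 | 0 |
| 75% | 80 − 60 = 20 | 20 | 80 − 75 = 5 | 20 | 15 |
| 90% | 80 − 60 = 20 | 20 | 80 − 90 = −10 | 20 | 30 |

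Under Table 1 the three situations look the same, and the step from acceptability to contact is 60 − 60 = 0 whatever the willingness. Under the article's definitions they can be told apart. The 20-point shortfall in use is visible either way.

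**Step 3. A stock-out of screening supplies (all inputs assumed).** Suppose 95% of women agree to a test and supplies are present on 60% of days. Other promotive care is ignored, although the actual indicator combines it with screening.

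- If staff still offer the test on stock-out days, use is 0.95 × 0.60 = 0.57. Acceptability and contact both read 57%, and availability can read 100%.
- If staff stop offering on those days, accessibility falls to about 60%. The gap then appears on the service side, though still not as a supply gap.

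How a shortage shows up therefore depends on staff behaviour, and no listed indicator measures it directly.

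**The case against.** A reader might infer that these bottlenecks cannot be detected at all, or that supply failures will be treated as women's unwillingness. The documents support neither.

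- Low use and low offer each register as a gap against target. The loss is in attribution, not detection.
- Root-cause analysis lies between gap and action. The team that does it includes providers, managers and service users, and may well find a stock-out.
- The *Formative evaluation* plans acceptability, feasibility and readiness surveys and qualitative work on barriers. The *Outcome (summative) evaluations* repeat the surveys and add patient satisfaction.
- The FCM column separates offered, consented, administered and administered per protocol, all among eligible women. An FCM stock-out would show as a low offer or as a drop from consent to administration, so the essential-drug-list remark supports the duplication point least.
- Effective coverage, the primary outcome, has its own row and definitions.
- The article says only that Table 1 highlights the indicators, and the bottleneck analysis tools are not shown. An unlisted commodity indicator cannot be excluded.

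All of this stands and limits the consequence. It does not remove the conflict between definition and indicator. Equating contact with acceptability is a stated rule, not a detail left to a fuller document. Surveys and interviews do not give a quarterly proportion to set against a target, and the article does not say who completes the surveys.

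**Conclusion.** The point holds in limited form. In two of three columns acceptability is measured as use and contact is set equal to it, so the quantitative measure cannot separate unwillingness from willing-but-not-served. In all three columns the published availability indicator covers only the staff half of its stated domain, so no listed indicator measures a shortage directly.

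The first part is firm, because it rests on the wording of Table 1. The second is less certain, because the full protocol's tools are not at hand. The numerical examples use assumed values and show only the mechanism. The equal gaps in Step 2 also assume one target for both domains. The defect concerns monitoring indicators and does not change the primary outcome. It is worth correcting because these indicators steer each quarterly cycle.

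**What to change.** 1. In the preventive/promotive and existing-management columns, define acceptability as the proportion of eligible women who agreed to the test or treatment, and contact as the proportion of the same eligible women who were actually tested or started on treatment. This copies the FCM column's split. The denominator must be the same in both rows, or the step between them cannot be read. Accessibility continues to show who was offered. State whether eligible women are the same women counted there (clinic attenders, and women diagnosed with anaemia); if they are, acceptance among those offered also follows. In the first case of Step 3, acceptability would read 95%, contact 57%, and the step 95 − 57 = 38 points.

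2. Add a commodity indicator to each availability cell, for example the percentage of facility-days in the quarter with the relevant supplies in stock, read from stock cards. If the full protocol's bottleneck tools already contain one, list it in Table 1 instead.

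The cost is a wording change in Table 1, an agreed/declined entry in the register (the article expects about 4000 women screened a year), and a quarterly stock-card reading at six sites. The last assumes that the sites keep stock cards, which the article does not state. The change is best made before baseline, since the Table 1 indicators are described then and a later redefinition would break the comparison over time.

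### The primary indicator for screening is a proportion of women already screened, so it does not respond to screening uptake

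*Protocol article*

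**What the plan says.** Under 'DIVA processes and outcomes', the article takes its outcomes from the Tanahashi model. It argues that coverage should "measure the percentage of the number of people who received quality service", and it defines effective/quality coverage as the "proportion of the target population who received quality and/or satisfactory service".

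Under 'DIVA outcome measures', it states: "The primary outcome of the DIVA process will be the improvement in the implementation fidelity (effective coverage) to the three management processes". The first of the three processes listed is screening, in pregnancy and after delivery.

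Table 1 then gives the operational definitions. In the effective/quality coverage row, preventive/promotive column, the indicator is "The proportion of eligible women screened for anaemia who adhered to the post-screening plan". The row carries the footnote "Primary outcome of DIVA". In the same column, the Acceptability row is "The proportion of eligible women who were screened and who utilised other promotive care provided", and the Contact row repeats it. Neither carries the footnote.

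'Outcome (summative) evaluations' uses the Table 1 effective coverage measures again as the primary outcome at end line.

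**The concern.** The text defines effective coverage over the target population, but the primary cell for screening is computed among women who have already passed the step that the study wants to strengthen. Failure to screen an eligible woman never counts against this indicator, and success in reaching her does not by itself count in its favour.

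Strengthening screening is the subject of the first objective and part of the last. The same measure serves twice. It is a DIVA indicator, for which the gap between target and observed coverage defines the bottleneck each quarter, and it is also the end-line primary outcome. A programme that extends screening could therefore see no change or a decline in its primary screening measure. The quarterly gap for that cell would not show the improvement either.

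**Working it through.** The article states no target, expected value or sample size for this indicator, so there is no figure of its own to reproduce. The check is algebra on the definitions. All rates below are assumptions chosen for illustration.

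**Notation**

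- s = women screened / women eligible for screening (uptake)
- a = women adhering to the post-screening plan / women screened
- Table 1 indicator = a
- Effective coverage over the target population = s × a

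The indicator does not contain s.

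**Effect of extending screening**

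Let uptake rise from s0 to s1. Women of the kind already reached keep adherence a0, and the added women adhere at rate m. Then:

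- coverage afterwards = s0·a0 + (s1 − s0)·m
- indicator afterwards = [s0·a0 + (s1 − s0)·m] / s1

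Coverage rises whenever m > 0. The indicator falls whenever m < a0. The two move in opposite directions for every m between 0 and a0.

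**Numbers**

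Example for m = 40%: coverage = 0.40 × 0.80 + 0.40 × 0.40 = 0.48; indicator = 0.48 / 0.80 = 0.60.

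| Assumed change | Table 1 indicator | Effective coverage |
|---|---|---|
| Uptake 40% to 80%, added women adhere at 80% | 80% to 80% | 32% to 64% |
| Uptake 40% to 80%, added women adhere at 60% | 80% to 70% | 32% to 56% |
| Uptake 40% to 80%, added women adhere at 40% | 80% to 60% | 32% to 48% |
| Uptake 40% to 80%, added women adhere at 20% | 80% to 50% | 32% to 40% |
| Uptake 30% to 90%, overall adherence 80% to 70% | 80% to 70% | 24% to 63% |
| Uptake 90% to 45%, overall adherence 60% to 80% | 60% to 80% | 54% to 36% |

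For the fifth row: 0.30 × 0.80 = 0.24 and 0.90 × 0.70 = 0.63. If women of the kind already reached keep 80% adherence, this implies that the added women adhere at (0.63 − 0.24) / 0.60 = 65%, so no extreme difference is needed. With uptake tripling, coverage would rise for any later adherence above 0.24 / 0.90 = 26.7%. The indicator would fall for any value below 80%.

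The last row is the reverse case: screening is halved, coverage drops by 18 points, and the indicator improves by 20.

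**What cannot be computed**

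'Study setting' projects about 4000 women screened and about 400 eligible for treatment per year. It does not give the number eligible for screening, so s is unknown and the distortion in this study cannot be sized.

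**The case against.** Four points can be made for the plan.

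1. *The wording may mean all eligible women.* The cell could be read as eligible women who were both screened and adherent. But the Acceptability cell in the same column, "The proportion of eligible women who were screened and who utilised other promotive care provided", joins the two conditions explicitly, and the primary cell does not. The conditional reading is the plain one. If both readings are open, the denominator of a primary outcome still has to be settled.

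2. *Uptake is measured elsewhere.* This is true and it limits the harm. Table 1 also tracks the offer of screening (Accessibility) and screening together with use of promotive care (Acceptability and Contact), and all domain indicators are described at baseline. A fall in the conditional ratio could be read beside them. But those rows are not primary, so they do not repair the primary outcome.

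3. *The indicator still responds to better care.* This also stands. Better follow-through after a test would raise it. A reader might infer that the indicator cannot show improved screening at all. That goes too far: what it misses is reach and uptake.

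4. *This is one of three primary indicators, and reversal needs a condition.* This is correct. A fall requires newly screened women to adhere less than those already screened, without an offsetting gain in follow-through. The article does not show that this will happen, so it does not support saying that the primary result as a whole will have the wrong sign.

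Two further readings are tempting but not supported. One is that the screening primary omits postpartum women who do not return to clinic. The clinic-attender denominator, "The proportion of women attending antenatal and postnatal clinics who were offered screening and promotive care", belongs to the non-primary Accessibility row, and the sentence beginning "After delivery, Hb levels should be measured within 24 to 48 h in women with blood loss above 500 mL" reports a WHO recommendation as background, not this study's screening rule. The other is that the FCM column shows the correct all-eligible basis. Eligibility for FCM rests on moderate to severe anaemia, normally established by a haemoglobin test, so unscreened women would usually be absent from that denominator too.

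**Conclusion.** The point holds for one cell of Table 1. The primary indicator for screening is, on its plain reading, conditional on having been screened. That conflicts with the article's own definition of effective coverage and with its statement that improved effective coverage of the screening process is a primary outcome. The indicator does not respond to uptake: at constant adherence, a doubling of uptake from 40% to 80% leaves it at 80% while coverage goes from 32% to 64%. With lower adherence among newly screened women it falls while coverage rises, as in 80% to 70% against 24% to 63%.

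The lack of response to uptake follows from the definition alone. The opposite movement rests on assumed rates, and its size in this study is unknown. Because the article already plans to monitor uptake in other rows and the repair is small, this should be fixed but does not undermine the study as a whole.

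**What to change.** Redefine the preventive/promotive cell in the effective coverage row as the number of women who were screened and adhered to the post-screening plan, divided by all women eligible for screening at the six facilities. State who counts as eligible, and use the same definition at baseline, in each quarterly cycle and at end line. Keep adherence among screened women as a secondary step indicator, so that a change in the primary can be split into uptake and follow-through.

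The cost is the rewording of one cell and a count of eligible women, which the Acceptability cell in the same column already calls for. The downside is a lower reported percentage whenever uptake is below 100%, and any quarterly target for this indicator has to be set on the new scale.
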